#### Multivariate analyses:

*Resting State Functional Connectivity:* Exercise-induced increases in CBF were previously associated with increased functional connectivity.(Burdette et al., 2010) Thus, we expect that in addition to an immediate positive impact on cerebral hemodynamics, acute and long-term aerobic exercise compared to stretching will increase rsFC, offering a potential mechanism for the cognitive benefits of exercise. We will use **machine learning methods** to analyze rsFC. A Riemannian manifold geometry-based approach (Yamin et al., 2019, 2023, 2020) that employs geodesic distance based dominant set (DS) clustering will be utilized to summarize dynamic rsFC matrices and identify distinctive brain connectivity patterns corresponding to different sessions (T1 vs. T2) and conditions (AET+PMT, Stretching+PMT). This method offers an advantage over using Pearson correlation directly. The imposition of Euclidean metrics, as in the Pearson correlation analysis, on Riemannian manifold data, as represented by FC matrices, can limit the predictive power of the machine learning classifier. In contrast, using geodesic distance respects the unique properties of the symmetric positive definite (SPD) matrices that represent FC, accurately capturing the manifold structure. To prepare resting-state fMRI data for this

analysis, functional scans will be aligned to participants' high-resolution T1-weighted images and to MNI152 standard space using nonlinear registration with lesion weighting (Andersson et al., 2007; Jenkinson et al., 2002). Preprocessing will include robust motion correction carried out using XCPEngine (Ciric et al., 2017), which allows implementation of different schemes of motion correction, including ICA-AROMA (Pruim et al., 2015), shown to yield high network identifiability and low connection-distance dependence. We will further remove lesion-driven artifacts by inspecting individual-level independent variance components that spatially overlap with the lesion and removing them from analyses (Yourganov et al., 2018). We will extract timeseries data from the Gordon atlas ROI (Gordon et al., 2016) and conduct geodesic DS clustering on the dynamic FC matrices. We will then compute one geodesic reference connectome per resulting cluster and convert the FC into a vector by computing the geodesic distance of each FC matrix from each cluster's reference connectome. These vector representations will be used as input features to classify different MRI sessions (T1 vs. T2 (Aim 2) and T1 vs. T3 (Aim 3)) for each condition. As a final step, we will perform sensitivity analyses to validate a subset of features contributing most to classification accuracy. These features will represent unique FC patterns which highlight the changes across testing sessions (T1 vs. T2) and conditions (AET+PMT, Stretching+PMT). Using similar methods in our pilot study, we found widespread treatment-induced increases in rsFC in a subset of 94 Gordon ROI that spatially overlap with a reading network mask derived from the Neurosynth database (Yarkoni et al., 2011)

Additionally, there may be individual variability in the response to treatment. We will explore the role of individual factors on functional improvement during treatment by fitting a mixed linear effects model (MLM) to the data with participants' intercepts and slopes as random effects. Modeling individual variability via the MLM will allow us greater sensitivity in detecting treatment effects.

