## **2. OBJECTIVES OF THE STUDY**

This study has 3 objectives:

1. To determine if the proposed intervention will improve language outcomes.
2. To examine the immediate impact of aerobic exercise on cerebral circulation
3. To examine the neural mechanisms of sustained change in reading outcomes following the proposed intervention.

To address Objective 1, we will randomize 100 chronic (>3 months post-stroke) left hemisphere stroke participants to either the aerobic exercise (AET) or the stretching condition. The AET condition will complete 20 minutes of moderate intensity aerobic exercise in the form of stationary bike cycling prior to a 1.5-hour targeted reading treatment session using phono-motor therapy (PMT) (Kendall et al., 2019). The control condition will complete 20 minutes of light

stretching before each PMT session. Both conditions will also have a 5-min warm up and cold down. All participants will complete 40, 2-hour intervention sessions administered 3-5 times per week for 8-10 weeks. We will measure reading competence as the primary outcome, and naming, auditory comprehension, and spontaneous speech as secondary language outcomes using standardized and experimental tasks administered before and after the full course of treatment. We expect a condition by time interaction, such that the AET condition will improve more than the stretching condition from baseline to end of treatment.

To address Objective 2, we will ask participants to undergo 2 MRI scans, one at baseline and one following the first AET or stretching session. The scans will assess regional and whole brain cerebral blood flow and functional connectivity to determine the immediate impact of aerobic exercise vs. stretching on neural and vascular processes. A greater increase in cerebral blood flow is expected after aerobic exercise than stretching.

To address Objective 3, we will ask participants to complete language testing and a 3rd MRI scan after completing the intervention. We expect greater increases in cerebral blood flow, brain connectivity, and task-related activation in the AET condition compared to the stretching condition. These increases are expected to be most evident in areas supporting phonology and orthography-to-phonology mapping. The increased cerebral circulation and brain activity are expected to predict reading and other language outcome gains.

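### The resting-state connectivity analysis classifies sessions within each condition and names no test of aerobic exercise against stretching, although that contrast is the stated hypothesis

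*Protocol*

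**What the plan says.** **Hypothesis.** Section 5.C, under Multivariate analyses, predicts that "acute and long-term aerobic exercise compared to stretching will increase rsFC". Section 2 says the same for Objective 3: "We expect greater increases in cerebral blood flow, brain connectivity, and task-related activation in the AET condition compared to the stretching condition". Objective 2 also lists functional connectivity among the measures of exercise versus stretching, although the expectation written out there concerns cerebral blood flow.

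**Analysis.** In Section 5.C, T1 is baseline, T2 is the scan after the first exercise or stretching session, and T3 is the post-treatment scan. Dynamic connectivity matrices are clustered, and the features are formed by "computing the geodesic distance of each FC matrix from each cluster's reference connectome". These vectors are used to "classify different MRI sessions (T1 vs. T2 (Aim 2) and T1 vs. T3 (Aim 3)) for each condition". The last step is that "we will perform sensitivity analyses to validate a subset of features contributing most to classification accuracy", and the retained features are said to represent "unique FC patterns which highlight the changes across testing sessions (T1 vs. T2) and conditions (AET+PMT, Stretching+PMT").

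**Nearby text.** For the behavioural data, the same section does name the condition-by-session interaction as the criterion of improvement. The rsFC text has no equivalent. A mixed model is planned to explore individual factors in functional improvement. It is not tied to rsFC, and no condition-by-session term is named.

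**The concern.** The hypothesis asks whether connectivity changes more, and upward, under exercise than under stretching. The classifier asks whether two scan sessions can be told apart within the exercise arm and, separately, within the stretching arm. Those are different questions. The results available at the end would be two accuracies, and the natural way to read them is to see which exceeds chance. If one does and the other does not, it is easy to conclude that exercise altered connectivity, yet no test of that difference has been made.

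For T1 vs T3 there is a further difficulty. Both arms receive the full PMT course between those scans, so a classifier that separates them within an arm may be detecting PMT, elapsed time or exercise. Only a comparison between the randomised arms isolates exercise.

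The prediction is also of an increase. Accuracy has no sign, and the protocol describes no step that recovers one.

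**Working it through.** The protocol gives no expected accuracy, significance level or power for the rsFC analysis, so there is no stated figure to reproduce. The check has four parts.

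**1. Question against analysis**

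| | Hypothesis | Analysis as described |
|---|---|---|
| Contrast | exercise vs stretching | T1 vs T2, T1 vs T3 |
| Level | between conditions | within each condition |
| Sign | increase | none (accuracy) |

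No later step joins the two columns. For T1 vs T3, each arm has 40 sessions × 1.5 h = 60 h of PMT between the scans.

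**2. What two within-arm tests can suggest (illustration)**

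Input from Section 2: 100 participants in total. Assumptions not in the protocol: 50 per arm, one paired session decision per participant, independent decisions, and a one-sided 5% exact binomial test against 0.5 in each arm.

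- Cut-off: the smallest r with P(X ≥ r | n = 50, p = 0.5) ≤ 0.05 is r = 32 (64% correct), with exact level 0.032.
- Power within an arm at true accuracy p: w = P(X ≥ 32 | n = 50, p).
- Chance that exactly one arm is significant when both share the same p: 2w(1 − w).

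| True accuracy, both arms | w | 2w(1 − w) |
|---|---|---|
| 0.50 | 0.032 | 0.06 |
| 0.55 | 0.127 | 0.22 |
| 0.60 | 0.336 | 0.45 |
| 0.65 | 0.622 | 0.47 |
| 0.70 | 0.859 | 0.24 |
| 0.75 | 0.971 | 0.06 |

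The expression cannot exceed 0.5, and it comes close to that near accuracy 0.63 (w = 0.505). By symmetry, half of each figure is the pattern that favours exercise: 0.11 at 0.55, 0.22 at 0.60 and 0.24 at 0.65.

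Counting 100 independent scans per arm instead gives a cut-off of 59 and 0.37, 0.47, 0.16 and 0.01 at accuracies 0.55, 0.60, 0.65 and 0.70. The size depends heavily on these choices.

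**3. Direction**

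Take 6 nodes with a common correlation r and a reference connectome with correlation r0. The affine-invariant geodesic distance is √{5·ln²[(1 − r)/(1 − r0)] + ln²[(1 + 5r)/(1 + 5r0)]}.

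- With r0 = 0.30, a rise to 0.40 gives √(5 × 0.0238 + 0.0332) = 0.390. A fall to 0.195 also gives 0.390. One distance carries no sign.
- With a second reference at 0.60, the same two matrices lie at 0.95 and 1.71. Several distances together can therefore hold directional information, but it has to be extracted.

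**4. Power of a direct between-arm comparison of accuracies**

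Power = Φ[(|p1 − p2| − 1.96·se0)/se1], with se0 = √[2p̄(1 − p̄)/n] and se1 = √{[p1(1 − p1) + p2(1 − p2)]/n}, two-sided 5%, n = 50 assumed.

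- 0.60 vs 0.80: se0 = 0.0917, se1 = 0.0894, (0.20 − 0.1796)/0.0894 = 0.228, power 0.59.
- 0.60 vs 0.75: power 0.36.
- 0.60 vs 0.70: power 0.18.

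For 80% power, 0.60 vs 0.80 would need 82 per arm and 0.60 vs 0.75 would need 152.

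**The case against.** **The text does look towards conditions.** Section 5.C says that the clustering should reveal patterns belonging to sessions and conditions, and that the selected features will highlight changes across both. A statistical analysis plan, not shown here, could attach a test to that. The intent is clear and nothing rules out a between-condition comparison. But the protocol goes further than leaving the test open: it specifies, aim by aim, a classification that does not address its hypothesis. That much stands as a finding.

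**The illustration uses a decision rule that the protocol does not state.** This is correct. Section 5.C contains no binomial test, cut-off or rule of one arm significant and the other not. The figures show why such a reading would mislead; they are not a false-positive rate of this plan.

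**Direction may be recoverable.** A reader might infer that the method cannot show direction at all. That goes too far: distances to several references, or inspection of the reference connectomes, may show it. The protocol also reports that "Using similar methods in our pilot study, we found widespread treatment-induced increases in rsFC", but it does not describe the step that gave the sign.

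**Circularity.** A reader might infer, from clustering being listed before classification and from the plan to "validate a subset of features contributing most to classification accuracy", that accuracies will be optimistic because training and test data are mixed. The protocol is silent on folds and held-out data. Any such pipeline, including a properly nested one, would be listed in this order, and the detail commonly belongs in an analysis plan. The documents do not support the inference.

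**T1 vs T2.** The PMT argument does not carry over to this pair, because the T2 scan follows the first exercise or stretching session rather than the treatment course. The lack of a between-arm test applies to both pairs.

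**Conclusion.** The concern holds for the rsFC analysis as written. A directional between-condition hypothesis is paired with a within-condition session classifier, and no described step tests exercise against stretching or extracts the sign of the change. This conclusion rests on the wording alone and needs no assumption.

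The size is illustrative. Under the assumptions of 50 per arm, 50 paired decisions and a one-sided 5% test in each arm, equal true accuracy yields exactly one significant arm in about 22% to 50% of trials for accuracies from 0.55 to 0.65, falling to 6% at 0.75.

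A reader might infer that Objectives 2 and 3 cannot be answered. The documents do not support this. The expectation stated for Objective 2 is about blood flow, which has its own repeated-measures and permutation analyses. Connectivity is one of three neural measures in Objective 3. The primary reading outcomes have an explicit condition-by-session interaction. Only the connectivity part of the two objectives is affected, so the change is advisable but does not touch the trial's main conclusion.

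**What to change.** 1. Make the rsFC test a between-condition one. Either classify condition from each participant's change in the distance vector (T2 − T1 and T3 − T1, measured against one common set of reference connectomes), or test the difference between conditions in session-classification accuracy. In both cases, take the p-value from a permutation that shuffles condition labels between participants and keeps each participant's scans together.
2. Add one signed connectivity summary, for example mean connectivity in the 94-region reading-network subset that the protocol already cites from its pilot, compared between conditions with adjustment for its T1 value. The protocol's argument against Euclidean measures concerns the predictive power of the classifier. A single signed summary beside the classifier does not conflict with it and supplies the direction that the hypothesis needs.
3. Report the within-condition accuracies as descriptive, with no inference from one arm exceeding chance while the other does not.

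The cost is some wording and computing time, with no new scans or participants. The real drawback is power. A direct comparison of accuracies has power of about 0.18 to 0.59 for the differences in the working, at an assumed 50 per arm, so a null result should be reported with its uncertainty and not as evidence of no effect.

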## 6. WORK SCHEDULE

|                                             |                            |
|---------------------------------------------|----------------------------|
| Participant Recruitment and Data Collection | Summer 2024-Fall 2028      |
| Data Analysis                               | Fall 2028-Spring 2029      |
| Preparation of conference presentations     | Summer 2025-Winter 2029    |
| Preparation of manuscripts                  | Fall 2028 2018-Winter 2029 |

## 7. PUBLICATION OF RESEARCH

The results of this study will likely be of interest to a broad audience of researchers in psycholinguistics, neuroimaging, neuropsychology, neurology, and speech & language pathology. We will submit manuscripts resulting from this work to peer-reviewed journals, with

the specific outlet to be determined by the target audience and anticipated impact of the findings. Findings will also be presented at top-tier professional conferences such as the Society for Neuroscience, the Society for the Neurobiology of Language, Cognitive Neuroscience Society, and the Organization for Human Brain Mapping. The PI and Co-Is will co-author the publications and RM, MC, and RAs will be listed as co-authors if their contributions qualify them as such. The authorship order to be determined based on the respective roles played in planning, conducting, and reporting the study. Preparation of conference presentations will be ongoing, and preparation of manuscripts will commence upon the completion of the study, as detailed in the work schedule.

